| Enrollment         | Within 14 days prior to the baseline visit or at the time of the visit, the | Not applicable | 
 
Judging criteria for admission to the platoon
 
informed consent of the patient
 
                                                                                                                                                                                                                                                                                                                                                                                                                                                                                                                                                                                                                                                                                             |
| Baseline visits    | Within 2 weeks prior to the combined surgery                                | Not applicable | 
 
baseline information and physical examination
 
Assessment of stroke risk (CHA2DS2-VASc score) and bleeding risk (HAS-BLED score)
 
history of atrial fibrillation
 
history of prior stroke/thromboembolism/bleeding
 
History of comorbid cardiovascular diseases such as hypertension/heart failure/cardiomyopathy, diabetes mellitus, and peripheral vascular disease
 
Medication history (including oral antithrombotic drugs §, AAD)
 
12 lead ECG and/or 24h Holter ECG data
 
TTE assessment (LA, LVEDd, LVEDs, LVEF)
 
TEE or CTA to exclude thrombus
 
baseline blood counts, liver function, renal function, coagulation, troponin, cardiac enzyme profile
 
             |

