#### 8.7.5 Patient's history of AF

- ✓ Record the date (year) of the patient's first episode of AF.
- ✓ Record the number of previous resuscitations for atrial arrhythmias.

- ✓ Documentation of the patient's arrhythmias other than atrial fibrillation.
- ✓ Evaluate CHA2DS2-VASc score and HAS-BLED score;

8.7.6 ECG information: provide recent ECG information (heart rate, rhythm, QT information, overall results);

8.7.7 Record the hospitalization records of the baseline visit and improve the baseline CRF. Try to notify the person in charge within 14 days of the visit. CRF must be authorized by the principal or representative.

Note: "Recent" means within the month of selection.

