### 8.8.6.2 Atrial Fibrillation Ablation Procedures

For paroxysmal atrial fibrillation, bilateral pulmonary vein isolation (PVI) was performed, and a single circle isolation rate was recorded. The mapping and ablation of spontaneous and/or induced (atrial high-frequency stimulation or intravenous injection of isoproterenol) non-pulmonary vein trigger focus were followed. Verify bilateral pulmonary vein bidirectional conduction block. For spontaneous or induced atrial fibrillation during operation, and ablation or intravenous injection of AAD (such as amiodarone needle or ibutilide needle) can not convert to sinus rhythm, synchronous DC cardioversion is performed.

For non-paroxysmal atrial fibrillation (persistent atrial fibrillation and long-term persistent atrial fibrillation), bilateral PVI was performed and the single circle isolation rate was recorded. The ablation of non-pulmonary vein trigger focus and individualized improvement of the left atrial matrix were performed. Specific matrix improvement strategy can refer to "STABLE-SR" matrix improvement strategy LAA electrical isolation is feasible for patients with a clear trigger focus of LAA Verify bilateral pulmonary veins and bidirectional conduction block of each ablation line. For spontaneous or induced atrial fibrillation during operation, and ablation or intravenous injection of AAD (such as amiodarone needle or ibutilide needle) can not convert to sinus rhythm, synchronous DC cardioversion is performed.

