## 9. Statistical methods

The random grouping order and statistical analysis of this study were conducted using SPSS software (IBM, USA, version 26.0).

Continuous variables that conform to the normal distribution are expressed as mean  $\pm$  standard deviation, and those that do not conform to the normal distribution are expressed as median (interquartile range IQR). The comparison between groups is performed by t-test or analysis of variance; Classified variables are expressed in terms of rate or composition ratio, and compared between groups  $\chi^2$  Inspection; The results of all time event variables are represented by the median survival time; Kaplan Meier analysis was used to compare the survival rates of the primary endpoint events and the events without atrial fibrillation/ATA between the two groups. COX regression analysis was performed for subgroup analysis of primary endpoint events, and was represented by forest map.  $P < 0.05$  was statistically significant.

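### Section 9 compares the arms by Kaplan-Meier with no covariate or stratum, although prognostic baselines are already collected; a small prespecified adjusted Cox model would be at least as efficient

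*Protocol*

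**What the plan says.** Protocol Section 9 gives one between-arm method for the primary composite: "Kaplan Meier analysis was used to compare the survival rates of the primary endpoint events". Freedom from AF/ATA is handled by the same method. Cox regression has a single role: "COX regression analysis was performed for subgroup analysis of primary endpoint events", shown as a forest plot. Section 9 names no covariate, stratum or overall hazard ratio.

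Section 8.8.2 and the randomisation row of Table 1 (Section 8.1) describe central computerised allocation by serial number at 1:1. No stratification factor is named.

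The baseline row of Table 1 lists both risk scores, the "history of atrial fibrillation", and a transthoracic echocardiogram that includes left atrial diameter. Section 3.2.2 sets the observed thromboembolic and bleeding events against the incidence that the two scores predict. Both kinds of event are components of the primary composite in Section 3.1.

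**The concern.** The protocol treats the two scores as predictors of events that belong to its primary endpoint, and collects them for every patient, but does not use them in the comparison of the arms. Allocation does not balance them except by chance.

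Two things are at stake, both modest. In a survival comparison, leaving out a prognostic baseline usually costs some power. And if the arms happen to differ visibly on a risk score, the reader is left with an estimate that has not taken this into account. An adjustment chosen after the imbalance has been seen carries little weight, so the model is best written down beforehand.

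As Section 9 stands, the subgroups would have model-based hazard ratios while the main comparison has no stated effect estimate.

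**Working it through.** **Inputs from the protocol.** Section 7: two-sided alpha 0.05, power 0.80, 1:1 allocation, 71 per group before loss, 20% loss, 89 per group after loss, 101 per group planned (202 in all). Section 5.2.4: 12 months of follow-up.

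**The plan's own figure.** 71 / (1 − 0.20) = 88.75, which rounds up to 89, as stated. The 71 cannot be reproduced, because Section 7 gives no difference, standard deviation or event rate. Every power figure below therefore rests on assumed values.

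**Chance imbalance.** For a baseline scaled to SD 1 with 101 per arm:

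- Standard error of the difference in means = sqrt(2/101) = 0.141.
- 95% range = ±1.96 × 0.141 = ±0.28 SD.
- Effect on the hazard ratio at that limit: exp(0.276 × ln 1.5) = 1.12 if the score carries a hazard ratio of 1.5 per SD, and exp(0.276 × ln 2) = 1.21 if it carries 2.

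For scale, with about 47 events the standard error of the log hazard ratio is about 2/sqrt(47) = 0.29. The shifts above are ln 1.12 = 0.11 and ln 1.21 = 0.19, or about 0.4 and 0.7 of a standard error.

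**Power.** Simulation assumptions: 202 patients, exponential times, censoring at 12 months, treatment hazard ratio 0.45, one standard-normal baseline score, 3000 trials per row. The unadjusted log-rank test is compared with the Wald test from a Cox model adjusted for the score.

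| Control 12-month event rate | Score HR per SD | Unadjusted | Adjusted | Change (points) |
|---|---|---|---|---|
| 30% (45 to 47 events) | 1.0 | 74.5% | 73.7% | −1 |
| 30% | 1.5 | 73.2% | 73.9% | +1 |
| 30% | 2.0 | 70.6% | 75.0% | +4 |
| 30% | 3.0 | 62.1% | 76.6% | +14 |
| 15% (about 22 events) | 1.0 | 46.2% | 43.1% | −3 |
| 15% | 1.5 | 42.5% | 40.0% | −2 |
| 15% | 2.0 | 41.5% | 41.6% | 0 |
| 15% | 3.0 | 39.2% | 42.4% | +3 |

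Part of the small loss in the weak-predictor rows comes from setting a Wald test against a score test. With likelihood-ratio tests in the simulation (treatment hazard ratio 0.5, control rates 15% and 30%), adjustment gains about 0 to 5 points and shows no material loss.

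**Validity.** Under no treatment effect, the unadjusted test rejected in 4.7% to 5.7% of simulated trials of 202 patients.

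**The case against.** The strongest reply is that nothing in Section 9 is wrong. An unadjusted comparison of randomised arms is valid, and its confidence interval already allows for chance imbalance. Covariate lists are often left to the statistical analysis plan, which is not at hand. Section 9 neither calls its comparison unadjusted nor rules out an adjusted one. With few events, adjustment gains little: at about 22 events, a model with arm and three covariates has only about 22/4 = 5.5 events per parameter.

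Most of this stands, and it makes the point an efficiency recommendation. It does not remove the point. Section 9 does more than leave the model open: it assigns Kaplan-Meier to the main comparison and Cox to the subgroups, so a later plan with an adjusted primary model would change a stated choice. The small-events argument limits the number of covariates; it does not argue against having any.

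A reader might infer more than the documents support, in four ways:

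- **That the unadjusted result is biased.** It is not. Imbalance under randomisation is random error, and the type I error holds.
- **That power is plainly given away.** This depends on prognostic strength and event count. The gain is near zero for weak predictors or few events.
- **That the baselines are strong predictors.** No figure in the protocol says so. Eligibility narrows two of them: CHA2DS2-VASc of at least 2 (3 for women) and left atrial diameter of at most 55 mm. The composite also includes device-related thrombosis and cardiovascular death or rehospitalisation, which Section 3.2.2 does not tie to the scores.
- **That AF type would be assigned at the operation, once the arm is known.** Section 8.7.5 asks investigators to "Record the date (year) of the patient's first episode of AF" and does not itemise paroxysmal against non-paroxysmal AF. But Table 1 collects AF history at baseline, and Section 8.7 places all baseline work before the procedure. Section 8.8.6.2 selects the ablation by AF type without saying when the type is determined, and Section 8.8.7.7 sends the occlusion-first arm to the same scheme.

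**Conclusion.** The point holds as a recommendation, not as an error. Section 9 names Kaplan-Meier, with no covariate or stratum, as the only between-arm method for the primary composite and AF/ATA freedom, and allocation names no stratification factor. The comparison is valid. A prespecified adjusted model would be at least as efficient: about 0 to 5 power points with moderate predictors, and up to about 14 in the most favourable setting tried (hazard ratio 3 per SD, 30% control event rate). It would also protect the estimate from a visible imbalance. At the 95% limit for one score, such an imbalance could move the hazard ratio by a factor of about 1.12 to 1.21.

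These sizes rest on assumed control event rates of 15% and 30%, treatment hazard ratios of 0.45 or 0.5, and the assumed prognostic strengths. The protocol supplies none of them.

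**What to change.** In Section 9, before any outcome is compared by arm:

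- Prespecify an overall Cox hazard ratio for the primary composite, with arm, CHA2DS2-VASc and HAS-BLED as terms.
- Prespecify the same for AF/ATA freedom, with arm and left atrial diameter. Add AF type where the baseline AF history, recorded before randomisation, gives it.
- Add no further covariates, because events may be few. At about 22 events, the three-term primary model already has only about 22/3 = 7 events per parameter.
- Report the Kaplan-Meier curves and the unadjusted result alongside.
- State that the adjusted hazard ratio is a conditional estimate. It need not equal the marginal, unadjusted one even when the arms are perfectly balanced.

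The cost is wording in Section 9. Both scores and left atrial diameter are already collected. The small downside is the change from a marginal to a conditional estimate, which reporting both results covers.

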## **10. Benefits of Study**

### **10.1 Benefits to participants**

#### **10.1.1 Economic benefit to the participants**

This is an investigator-driven, prospective, randomized, controlled registry study in which the surgical instruments used and the surgical strategies employed are routinely used in clinical practice, and subjects are not required to take on additional risks beyond real-world surgical risks; therefore, there is no compensatory economic benefit to all subjects.

#### **10.1.2 Medical benefits for the participants**

In this study, we designed a strict and scientific intraoperative surgical plan for the subjects by the recommendations of the current guidelines for the treatment of atrial fibrillation and the consensus of clinical experts, as well as a well-thought-out and reasonable postoperative follow-up plan, which provided a technical guarantee to maximize the clinical benefits of the subjects after the operation.

### **10.2 Benefits to the Researcher**

#### **10.2.1 Economic benefits to the researcher**

This study is an investigator-initiated multicenter clinical study, in which the head of the center where the study is conducted and the relevant clinical staff will participate and facilitate the implementation of all study procedures. The sponsor of the study (Ningbo First Hospital) will provide financial subsidies to all the investigators who have contributed to the study on a case-by-case basis.

#### **10.2.2 Academic benefits for researchers**

All study data will be made available to all Participating Centers for analysis of clinical data and preparation of multicenter Study papers after the last subject is followed up. Participating centers will be allowed to co-sign all Study results involving multicenter-related data (see Section 11.6 for details).

## **11. Study of risks and risk avoidance**

There is no data to confirm a higher risk of one of the 8.2 partial adverse events than the other between the two combining strategies involved in the study. In our experience, the two combining strategies do not increase the current procedural risk.

## 12. Organization information

### 12.1 Functioning of the Study Organization

[name] of the First Affiliated Hospital of Ningbo University and the Ningbo First Hospital, Ningbo, China, was responsible for initiating, executing, and coordinating the study

12.1.1 The responsibility of the person in charge shall comply with the provisions of ISO14155;

12.1.2 As the study facilitator, Boston Scientific coordinates and helps the study enrollment and follow-up;

12.1.3 This includes but is not limited to, the following activities.

12.1.3.1 Recognition of Clinical Investigators;

12.1.3.2 Activation of the Study center when the required documentation is complete.

12.1.3.3 Development and analysis of Study databases;

12.1.3.4 Signing of the study plan before the commencement of the study or after the program has been adjusted;

12.1.3.5 Review of collected data and Study documents to assess the degree of completion and accuracy of the Study.

12.1.3.6 Ensure that all adverse events and device-related adverse events are reported and analyzed retrospectively by the clinical investigator; all serious adverse events and device-related serious adverse events are reported to the relevant experts, ethics committees, and/or safety monitoring committees.

### 12.3 The researcher

The investigator is defined as the individual and/or organization responsible for performing the clinical study and/or for safeguarding the interests associated with the responsible subjects.

#### 12.3.1 Researcher Responsibility

Upon consenting to the protocol, investigators will be subject to Study-related monitoring, audits, ethics committee reviews, and coordinator visits. They may also be given direct access and copying of study data and records by authorized individuals, provided that patient consent is obtained and patient privacy is protected.

12.3.1.1 Provide written authorization from the investigator/co-investigator.

12.3.1.2 Provide informed consent approved by an ethics committee.

12.3.1.3 Follow the consent letter signed by Ningbo First Hospital, the Study plan, relevant laws and regulations (such as ISO14155), and the consent letter proposed by the Ethics Committee or relevant coordinating authority for the Study;

12.3.1.4 Collecting and storing data from postoperative and follow-up examinations;

12.3.1.5 Screening and Enrollment of suitable patients;

12.3.1.6 Support the work of the monitors and reviewers (if any) to ensure the strict implementation of the clinical investigation plan (CIP), confirm the original data, and identify and correct the inappropriate or missing data in the CRF.

#### 12.3.2 Researcher's Folder

Researchers will be provided with an Investigator Study Binder (ISB) at the beginning of the study. This folder contains the relevant files required for the study.

### 12.4 Ethical Foundations

The study will follow the Helsinki Declaration of the International Medical Organization, ISO 14155, and all local laws and regulations.

Before the start of the study, the clinical Study plan will be submitted to the relevant Ethics Committee (EC)/Institutional Review Board (IRB) for review together with the relevant documents (patient information sheet, patient information letter). EC/IRB approval documents shall include the following contents:

- Date of the meeting.
- Composition of the Committee and list of participants and voters.
- Clinical Study Program Audit Edition;
- Patient Information and Informed Consent Review Edition.

EC/IRB approval documents must be prepared before the study starts. Any revision of the protocol should be submitted to the EC/IRB. According to local and national regulations, serious adverse events and device-related adverse events should be notified to EC/IRB.

## **12.5 Supervision**

As the initiator of the study, Ningbo First Hospital has the responsibility to ensure the strong supervision of the Study process, to ensure the smooth implementation, recording, and reporting of the study by the requirements of CIP, the signed clinical study consent, and relevant laws and regulations. The supervision process shall be carried out in the Study center according to the standard operating procedures and work guidance process.

## **12.6 Raw data disclosure**

The original data will be disclosed to all centers participating in the study within 6 months after the study is completed, in the form of sharing CRF form record results and preliminary statistical results of all data of the study.

## **12.7 Study reports and publication policy**

At the end of the study, a clinical and statistical report should be prepared by the study leader in consultation with the other co-investigators.

The first publication should cover the full range of data from the Study center. Publication of any part or all of the findings (journal or newspaper abstracts, oral presentations, etc.) by or on behalf of the investigator should be approved by the Head of Study prior to submission. To protect intellectual property rights, the Director reserves the right to delay publication. The first published article will be written by the sponsor center as the corresponding author and by the top 3 centers with the highest number of enrolled

cases as the co-first authors. All authors will be listed in descending order of the number of cases enrolled in the study, or if the number of cases is the same, the order will be based on the time of completion of enrollment.

## 13. Appendix A: Abbreviations

| Abbreviations | Description                                        |
|---------------|----------------------------------------------------|
| AAD           | Antiarrhythmic drug                                |
| ADE           | Adverse device effect                              |
| AE            | Adverse event                                      |
| AF            | Atrial fibrillation                                |
| AI            | Ablation index                                     |
| ATA           | Atrial tachyarrhythmia                             |
| CRF           | Case report form                                   |
| CS            | Coronary sinus                                     |
| CTA           | Computed tomography angiography                    |
| DAPT          | Dual antiplatelet therapy                          |
| DRT           | Device related thrombus, occluder related thrombus |
| EC            | Ethics committee                                   |
| ICE           | Intracardiac echocardiography                      |
| IRB           | Institutional review board                         |
| IRV           | Investigational required visit                     |
| ISB           | Investigator study binder                          |
| ISO           | International standards organization               |
| LA            | Left atrium                                        |
| LAA           | Left atrial appendage                              |
| LAAO          | Left atrial appendage occlusion                    |
| LSPV          | Left superior pulmonary vein                       |
| LVEDd         | Left ventricular end diastolic diameter            |
| LVEDs         | Left ventricular end systolic diameter             |
| LVEF          | Left ventricular ejection fraction                 |
| NOAC          | New oral anticoagulant                             |
| NYHA          | New York Heart Association                         |
| PDL           | Peri device leak                                   |
| PI            | Principal investigator                             |
| PIC           | Patient informed consent                           |
| PVI           | Pulmonary vein isolation                           |

|      |                                  |
|------|----------------------------------|
| RFCA | Radiofrequency catheter ablation |
| SAE  | Serious adverse event            |
| SAPT | Single antiplatelet therapy      |
| TE   | Thromboembolism event            |
| TEE  | Transesophageal echocardiography |
| TTE  | Transthoracic echocardiography   |

## 15. Appendix C: Data Acquisition

|                               | Baseline visits     | Surgery | 12h after operation~before discharge | 45 days $\pm$ 7 days | March $\pm$ 14 days | June $\pm$ 14 days | December $\pm$ 14 days |
|-------------------------------|---------------------|---------|--------------------------------------|----------------------|---------------------|--------------------|------------------------|
| Entry table                   | √                   |         |                                      |                      |                     |                    |                        |
| Surgical tables               |                     | √       |                                      |                      |                     |                    |                        |
| Follow-up form *              |                     |         | √                                    | √                    | √                   | √                  | √                      |
| 12-lead electrocardiogram     | √                   |         | √                                    | √                    | On demand           | On demand          | On demand              |
| ambulatory electrocardiogram  |                     |         |                                      |                      | √                   | √                  | √                      |
| TTE                           | √                   |         | √ #                       |                      | √                   | √                  | √                      |
| TEE                           | √                   | √       |                                      | √                    |                     | On demand          | On demand              |
| Laboratory tests              | √                   |         | √                                    |                      | √                   |                    |                        |
| programmatic deviation tables | Fill in as required |         |                                      |                      |                     |                    |                        |
| Unscheduled visits            | Fill in as required |         |                                      |                      |                     |                    |                        |
| Adverse events table          | Fill in as required |         |                                      |                      |                     |                    |                        |
| Study the termination table   | Fill in as required |         |                                      |                      |                     |                    |                        |
| The death table               | Fill in as required |         |                                      |                      |                     |                    |                        |

Notes.

\*:The follow-up form includes a record of the patient's general condition and medication use.

#: It is only required to complete the pericardial cavity assessment, and complete TTE inspection can be performed as required.

Abbreviation: TTE, transthoracic echocardiography; TEE, transesophageal echocardiography.
